### **Clinical examination and blood samples**

Blood samples as specified in table 1 will be collected by a trained laboratory technician and treated according to set procedures.

### **Sample size considerations and statistical analyses**

This study is designed as an exploratory study. It is anticipated that 100 participants are likely to be included during a period of 6 months. A sample size of 100 individuals is considered sufficient to test the hypothesis: 'is there a difference between the reported BASDAI in SpA patients whether they are men or women? For a two-sample pooled t test of a normal mean difference with a two-sided significance level of 0.05, assuming a common standard deviation of 1.5 BASDAI units, a total sample size of 100 assuming a balanced design (1:1 male-female ratio) has a sufficient power (91%) to detect a mean difference of 1 BASDAI units.

All descriptive statistics and test will be reported in accordance with the recommendations of the "Enhancing the QUALity and Transparency Of health Research" (EQUATOR) network (36): the STROBE Statement (37). We consider p values less than 0.05 (and 95% confidence intervals excluding the null) to be statistically significant.

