## **Aims**

1. To analyze the distribution according to specific concomitant conditions in the SpA group:

Ankylosing spondylitis was diagnosed when the patients fulfilled the modified New York criteria (30), psoriatic arthritis was diagnosed when patients fulfilled the CASPAR criteria (31), enteropathic arthritis was diagnosed when patients exhibited inflammatory axial and/or peripheral

joint involvement associated to a confirmed IBD (Crohn's disease or ulcerative colitis), SpA was diagnosed when patients fulfilled the ASAS criteria (2), reactive arthritis was diagnosed when an asymmetric inflammatory oligoarthritis and/or inflammatory low back pain associated to confirmed genitourinary or gastrointestinal tract.

2. To characterize the extra-articular manifestations according to ASAS criteria, however also including the recently described nephrolithiasis among SpA patients:  
Anterior uveitis, (past or present), inflammatory bowel disease (past or present) enthesitis (past or present), psoriasis (past or present) dactylitis (past or present) and furthermore to assess other features as: urethritis, pyoderma gangrenosum, keratoderma blennorrhagica, erythema nodosum (past or present), nephrolithiasis (past or present), and urine components.
3. To estimate the male-to-female ratio among patients with SpA
4. To investigate faecal calprotectin in patients with any disease in the SpA spectrum
5. To analyze the influence of gender on self-reported disease activity:  
Estimation of disease activity and functional status is evaluated using BASDAI, BASFI and 36-Item Short-Form Health Survey (SF-36)
6. To analyze co-morbidity among SpA patients using Charlson Comorbidity Index

A priori hypotheses are as follows:

- A. The amount of self-reported disease activity is more pronounced in woman than in men

- B. Females are more likely to have peripheral joint involvement rather than axial compared to men
- C. Extra articular manifestations are more frequent seen in males compared with females
- D. Faecal calprotectin is higher in men than women
- E. Urine electrolytes are altered and related to nephrolithiasis and NSAID exposure

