| Disease Characteristics                                       |   |
| Symptom duration (months)                                            | X |
| Axial disease (yes/no)                                               | X |
| MRI positive (yes/no)                                                |   |
| Peripheral joint involvement (yes/no)                                | X |
| Medication                                                    |   |
| Prior NSAID (yes/no)                                                 | X |
| Current NSAID at assessment (yes/no)                                 | X |
| Prior DMARD therapy (yes/no)                                         | X |
| MTX dose (mg/week)                                                   | X |
| Other current DMARD therapy                                          | X |
| No. of previous biologics used (if any)                              | X |
| Name of current biological agent                                     | X |
| Dose of prednisolone orally at assessment (mg/week)                  | X |
| Intramuscular glucocorticoid injections in the previous 3 month (mg) | X |
| Clinical examination                                          |   |
| 46 swollen joint count                                               | X |
| 46 tender joint count                                                | X |
| BASMI                                                                | X |
| SpA features                                                  |   |
| Anterior uveitis, past or present (yes/no)                           | X |
| Inflammatory bowel disease, past or present (yes/no)                 | X |
| Psoriasis, past or present (yes/no)                                  | X |
| Preceding infection (yes/no)                                         | X |
| Total enthesitis count                                               | X |
| Dactylitis count                                                     | X |

|                                                                                                                                                                                                                   |   |
|-------------------------------------------------------------------------------------------------------------------------------------------------------------------------------------------------------------------|---|

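### The only comparison named for BASDAI in men and women is an unadjusted, equal-variance t test, while aim 5 asks about the influence of gender and the sex ratio is not controlled

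*Protocol*

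**What the plan says.** The Protocol section Sample size considerations and statistical analyses calls the study exploratory and sizes it on one question: "is there a difference between the reported BASDAI in SpA patients whether they are men or women". The calculation reads "For a two-sample pooled t test of a normal mean difference with a two-sided significance level of 0.05". It takes one SD of 1.5 units for both sexes and 100 patients split 1:1, and concludes that this "has a sufficient power (91%) to detect a mean difference of 1 BASDAI units". The rest of the section covers reporting under STROBE and the 0.05 threshold. It names no other comparison, model or covariate.

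Four other places bear on this:

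- **Aims, item 5:** "To analyze the influence of gender on self-reported disease activity". Item 3 makes the male-to-female ratio something to be estimated. Hypothesis B expects disease pattern to differ by sex: "Females are more likely to have peripheral joint involvement rather than axial compared to men".
- **Participants:** adults with any disease in the SpA spectrum seen in the department may enter. There is no restriction on sex, age range above 18, duration or treatment.
- **Table 1:** age, symptom duration, axial and peripheral involvement and medication are collected, down to "Name of current biological agent". None is given a role in the sex comparison.
- **Abstract, Method and analysis:** the clinical characteristics will be explored for an impact on BASDAI. The text does not say whether this is done jointly with sex.

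**The concern.** Aim 5 speaks of an influence, and the only named comparison delivers a crude difference between whoever attends the clinic. If the men and women seen there differ in age, and BASDAI varies with age, part of the crude difference is an age difference. Age is not caused by sex and is already recorded, so this part can be removed at almost no cost.

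The second weakness is the equal-variance form. The pooled t test tolerates unequal spread when the groups are about the same size, but not otherwise. The 1:1 split is an assumption of the power statement, and nothing in recruitment secures it. The Rationale section cites three men per woman in ankylosing spondylitis, while noting that the gap is less apparent under newer criteria.

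At stake is how the result for the one powered hypothesis may be read, and whether its p value keeps the nominal 5%.

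**Working it through.** **1. The plan's own figure.** Inputs from the sample-size section: 50 men, 50 women, difference 1, common SD 1.5, two-sided alpha 0.05.

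- SE = 1.5 × √(1/50 + 1/50) = 0.30, so the noncentrality is 1/0.30 = 3.33 on 98 degrees of freedom.
- Power from the noncentral t distribution is 0.910 (normal approximation 0.915). The stated 91% is reproduced.
- The same formula gives 87.4% at 67/33 and 81.6% at 75/25.

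**2. Pooled test when size and spread both differ.** Assumptions, not in the protocol: SD 1.5 in one sex and 2.0 in the other, equal means, N = 100.

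- True SE = √(s₁²/n₁ + s₂²/n₂).
- SE on which the pooled test centres = √{[(n₁−1)s₁² + (n₂−1)s₂²]/98 × (1/n₁ + 1/n₂)}.

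For 67 patients with SD 1.5 and 33 with SD 2.0:

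- True SE = √(2.25/67 + 4/33) = 0.393.
- Pooled variance = (66 × 2.25 + 32 × 4)/98 = 2.82, so pooled SE = √(2.82 × 0.0452) = 0.357. That is 9% too small.

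With the SDs swapped, the true SE is 0.358 and the pooled SE 0.394, which is 10% too large. Error rates by simulation:

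| Split | Larger SD in | Pooled t | Welch |
|---|---|---|---|
| 50/50 | either group | about 5% | about 5% |
| 67/33 | smaller group | 7.5% | about 5% |
| 75/25 | smaller group | 8.8% | about 5% |
| 67/33 | larger group | 3.1% | about 5% |
| 75/25 | larger group | 2.5% | about 5% |

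Repeated simulations agree to within a few tenths of a point.

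**3. Age mix.** The documents give no age distribution by sex and no relation of BASDAI to age, so only a range can be shown. Suppose an age band is more common in one sex by 0.1 to 0.3, and BASDAI in that band differs by 0.5 to 1.5 units. The shift in the crude difference is prevalence gap × BASDAI gap:

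- from 0.1 × 0.5 = 0.05 to 0.3 × 1.5 = 0.45 units;
- middle case 0.2 × 1.0 = 0.20 units.

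At 50/50 with SD 1.5 and no sex difference at a given age, the crude test would reject in 5.3% to 31.8% of studies (10.1% in the middle case). These figures show how the mechanism scales. They do not estimate what this clinic would show.

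**4. Cost of adjustment.** Let R² be the share of BASDAI variance explained by the covariates and Rₓ² the share of variance in sex that they explain. The residual SD is 1.5 × √(1 − R²), the effect scales by √(1 − Rₓ²), and one degree of freedom is lost per covariate. With four covariates at 50/50, power for an adjusted difference of 1 unit is:

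- 0.84 at R² = 0, Rₓ² = 0.2;
- 0.91 at R² = 0.2, Rₓ² = 0.2;
- 0.98 at R² = 0.3, Rₓ² = 0.

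At 67/33, R² = 0.10 with Rₓ² = 0 moves power from 87.4% to 90.5%. One hundred patients can support an adjusted estimate.

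**The case against.** The strongest reply is that the sentence about the t test is a power assumption. A reader might infer that the protocol binds the final analysis to an unadjusted pooled t test. It does not say so. Sizing on a simple test is usual and excludes no adjusted model, covariates are commonly set in a statistical analysis plan (none was available here), and the Abstract foresees examining other characteristics against BASDAI. This part of the objection stands, so what follows is conditional on the test being used as written.

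A reader might also infer that sex differences in phenotype, duration or treatment make the crude difference spurious. The documents do not support that. None of these factors causes sex, and they may lie downstream of it. The question in the sample-size section is whether reported BASDAI differs between men and women. A gap that arises because women have more peripheral disease is part of the answer, and rejecting on it is no type I error for that null. Adjusting for such factors asks a different question, about a direct difference. This also stands. It leaves age mix as the clearer source of bias for aim 5.

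Finally, the pooled test need not be anti-conservative. At equal group sizes it holds about 5%, and with the larger SD in the larger group it is conservative. The protocol itself assumes a common SD. This stands too, but an error rate that could fall on either side of 5% is still a reason to prefer Welch, which costs almost nothing.

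**Conclusion.** The point holds in a limited form. For its one powered hypothesis the protocol names only an unadjusted, equal-variance comparison, which fits poorly with aim 5 and with a sample whose sex ratio is left open. Used as written, the test would have a true error rate of about 2.5% to 8.8% for splits of 67/33 to 75/25, and about 5% at 50/50. These rates rest on assumed SDs of 1.5 and 2.0. The size of any age effect cannot be judged from the documents.

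No stated figure is wrong: 91% power is correct at 1:1. It does not follow that the analysis is confounded by phenotype or treatment, or that false positives are necessarily inflated. In an exploratory study this is a worthwhile improvement in method and does not put the design in doubt.

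**What to change.** Add a few lines to the sample-size and statistics section:

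1. Report the crude difference in mean BASDAI, women minus men, with a 95% confidence interval from Welch's method or robust standard errors. This answers the question as the sample-size section puts it.
2. Add a prespecified linear model of BASDAI on sex and age, with heteroscedasticity-robust standard errors, as the adjusted estimate for aim 5. State before the data are seen which of the two carries the test of hypothesis A.
3. Present models that also include symptom duration, diagnosis, axial or peripheral disease and current treatment as secondary and explanatory. Say that they describe how much of the sex difference runs alongside these factors, so they address a direct rather than a total difference.

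The covariates are already among the data to be collected, and the sample size can stay. The cost is a little extra analysis, one degree of freedom for age and a few more in the secondary models. Some precision is lost if age is strongly related to sex but hardly to BASDAI.

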### **DISCUSSION, ETHICS AND DISSEMINATION**

We will apply the ethics committee for the region of Southern Denmark.

Dissemination will occur through presentation and publication in international peer-reviewed journals.

Knowledge about the presence of extra-articular manifestations in an individual may be useful for rheumatologists to optimize the treatment.

This study is an attempt to evaluate the characteristics of the patients within the SpA spectrum regarding extra-articular manifestations, disease onset (age of onset, age of diagnosis, delay in diagnosis, and first symptom at presentation) clinical activity evaluated by ESR, CRP, BASDAI and BASFI. It is our hope that the

results of this study may add to the knowledge of the disease pattern among patients diagnosed with SpA.

**Figure 1** ASAS Classification Criteria for Axial Spondyloarthritis (SpA)

|                                                                                                                                                                    |    |                        |
|--------------------------------------------------------------------------------------------------------------------------------------------------------------------|----|------------------------|
| Sacroilitis on imaging*                                                                                                                                            | OR | HLA-B27                |
| Plus                                                                                                                                                               |    | Plus                   |
| ≥ 1 SpA feature                                                                                                                                                    |    | ≥ 2 other SpA features |
| *active inflammation on MRI highly suggestive of sacroilitis associated with SpA, or definite radiographic sacroilitis according to the modified New York criteria |    |                        |
| SpA features:                                                                                                                                               |    |                        |
| Inflammatory back pain                                                                                                                                             |    |                        |
| Arthritis                                                                                                                                                          |    |                        |
| Enthesitis                                                                                                                                                         |    |                        |
| Uveitis                                                                                                                                                            |    |                        |
| Dactylitis                                                                                                                                                         |    |                        |
| Psoriasis                                                                                                                                                          |    |                        |
| IBD*                                                                                                                                                               |    |                        |
| Family history for SpA                                                                                                                                             |    |                        |
| HLA-B27                                                                                                                                                            |    |                        |
| Elevated CRP                                                                                                                                                       |    |                        |
| Good reponse to NSAID                                                                                                                                              |    |                        |

[figure not shown]

**Figure 2** Overview of participant flow

\*Exclusion criteria: (1) No consent, (2) Does not understand Danish, (3) Age < 18 years

**Contributors:** [name] serves as the principal investigator for this study. [name], [name], [name] and [name] participated in the design of the study and drafting of the protocol

**Funding** The initiative for the project was taken by The Department of Medicine, Section of Rheumatology, Odense University Hospital, Svendborg. The project is funded by a PhD stipend from the PhD fund of Region Southern Denmark. The amount is 500.000 DKR and is covering 1 year salary (including 1 year study fee) to the PhD student. The investigator has no affiliation to the PhD fund of Region Southern Denmark. Additional funds will be applied. There will be no fees for the participants.

**Competing interests** None.

**Ethics approval** Will be approved by the southern region of Denmark's Ethics Committee and the Data protection at the Region of Southern Denmark.

